### Statistical analysis

The main analysis will be undertaken after 104 weeks of treatment; an interim analysis is planned after 52 weeks of treatment (Table 3). The non-inferiority of empagliflozin compared to glimepiride on the primary endpoint of change from baseline in HbA_1c_ will be tested after 52 and 104 weeks of treatment based on a one-sided significance level of 1.25%. In total, 698 patients per arm are required to provide a power of ≥95% to show non-inferiority, based on a margin of 0.3%, on the primary endpoint at 52 and 104 weeks at this significance level if the true treatment effect is 0.05% (adjusted for multiplicity related to the 52-week analysis), and the standard deviation is 1.2%.

**Table 3 T3:** Hierarchical statistical methods

	**Analysis**	**Testing hierarchy for 52-week analysis (interim analysis)**	**Testing hierarchy for 104-week analysis (main analysis)**
1	Primary	Non-inferiority in change from baseline in HbA_1c_	Non-inferiority in change from baseline in HbA_1c_
2	Secondary	Superiority in change from baseline in body weight	Superiority in change from baseline in body weight
3		Superiority in incidence of confirmed hypoglycemic AEs	Superiority in incidence of confirmed hypoglycemic AEs
4		Superiority in change from baseline in SBP	Superiority in change from baseline in HbA_1c_
5		Superiority in change from baseline in DBP	Superiority in change from baseline in SBP
6			Superiority in change from baseline in DBP

*Legend*: *HbA*_*1c*_ glycosylated hemoglobin, *AEs* adverse events, *SBP* systolic blood pressure, *DBP* diastolic blood pressure.

The superiority of empagliflozin compared to glimepiride on the primary endpoint will be tested after 104 weeks’ treatment. Other key secondary endpoints will be tested for superiority at weeks 52 and 104, based on a significance level of 2.5% (two-sided) (Table 3). All other exploratory tests, including all analyses conducted at 208 weeks, will be 2-sided at a 5% level (no multiplicity adjustment).

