The efficacy analyses will be performed on the full analysis set (FAS), i.e. all randomized patients who received ≥1 dose of study drug and had a baseline HbA_1c_ assessment, using the last observation carried forward (LOCF) methodology for imputation of missing data. Efficacy data after the first intake of rescue medication will be set to missing. For the primary endpoint, an analysis of covariance (ANCOVA) model will be used with randomized treatment, eGFR and geographical region as fixed effects and baseline HbA_1c_ as a covariate. Sensitivity analyses of the primary endpoint will be undertaken in the per-protocol set (PPS104: patients in the FAS without any important protocol violations during the first 104 weeks’ treatment, such as violating the inclusion or exclusion criteria, changing dose of background metformin IR, taking the incorrect trial medication, or compliance <80%), FAS104 completers (patients in the FAS who complete the 2-year treatment period and have HbA_1c_ values for the end of the treatment period) and PPS104 completers (FAS104 completers who do not have any important protocol violations) using the same model and the LOCF approach to missing data. Additional sensitivity analyses include a restricted maximum likelihood-based model repeated measures (MMRM) approach in observed cases in the FAS to determine the effect of empagliflozin on HbA_1c_ over time. Secondary endpoints will be analyzed using the same model as the primary endpoint, with the continuous baseline values of the endpoint being investigated included as an additional covariate. Blood pressure data after changes in antihypertensive medication will be set to missing and imputed using LOCF.

All safety endpoints will be analyzed in the treated set, i.e. all patients who received ≥1 dose of study drug and presented using descriptive statistics. Confirmed hypoglycemic events will be analyzed using Cochran-Mantel Haenszel tests stratified by baseline HbA_1c_ (<8.5% vs. ≥8.5%). Change from baseline in lipid parameters will be analyzed using ANCOVA. Time-to-event analyses (Kaplan-Meier) for onset of new microalbuminuria (albumin/creatinine ratio [ACR] ≥30 mg/g), onset of new macroalbuminuria (ACR ≥300 mg/g), and progression from microalbuminuria to macroalbuminuria groups compared using log-rank tests.

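### The primary HbA1c non-inferiority test relies on LOCF although the two drugs are expected to have different time courses, so it can be biased in either direction; the planned MMRM should be primary

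*Protocol article*

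**What the plan says.** All points are in the protocol article, Methods, Statistical analysis, unless stated otherwise.

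- Efficacy is analysed in the full analysis set "using the last observation carried forward (LOCF) methodology for imputation of missing data". The model behind the main test is stated thus: "an analysis of covariance (ANCOVA) model will be used with randomized treatment, eGFR and geographical region as fixed effects". HbA1c at baseline is the covariate.
- "Efficacy data after the first intake of rescue medication will be set to missing". Rescued patients therefore enter LOCF with their last value before rescue.
- Non-inferiority "will be tested after 52 and 104 weeks of treatment based on a one-sided significance level of 1.25" per cent. In Table 3 this test stands first in both hierarchies.
- The per-protocol and two completer analyses use the same model and LOCF. FAS104 completers are defined as patients who finish two years and have HbA1c values at the end of that period.
- "Additional sensitivity analyses include a restricted maximum likelihood-based model repeated measures (MMRM) approach in observed cases in the FAS".

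On time course, the Background describes sulfonylureas as effective at first but not durable, and speculates that empagliflozin may hold glycemic control longer. The endpoint list includes a coefficient of durability, a slope fitted from week 28 onward. Study design has glimepiride titrated up to week 12. The article gives no expected rate of dropout or rescue.

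**The concern.** LOCF gives the treatment difference at the tested week only if the difference does not change after the last value carried. This trial was set up to find out whether it changes. A patient who leaves or is rescued at week 28 contributes the week-28 response to the week-104 comparison, so the estimate mixes earlier differences with the one named in the endpoint.

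If empagliflozin loses ground late, LOCF brings in the smaller early differences and makes inferiority look milder than it is. If glimepiride loses ground, LOCF keeps its early response and hides part of an empagliflozin advantage. The first case threatens the error rate of the test on which every later test in Table 3 depends. The second costs power, chiefly in the week-104 HbA1c superiority test.

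**Working it through.** **Inputs from the article.** "698 patients per arm are required to provide a power of ≥95% to show non-inferiority", "based on a margin of 0.3"%, "if the true treatment effect is 0.05"%, SD 1.2%, one-sided alpha 1.25%. Results reports 1545 treated patients, about 772 per arm. HbA1c visits are those of Table 2.

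**The plan's own figure.** n per arm = 2 × 1.2² × (2.2414 + 1.6449)² / (0.3 − 0.05)² = 696 with the normal approximation. The noncentral t gives exactly 698 (power 0.950). The stated sample size reproduces.

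**Formula.** Write differences as empagliflozin minus glimepiride, so positive values favour glimepiride. Let m be the share of patients whose value is carried forward and e the mean difference in the carried values. With the true week-104 difference at the margin:

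- LOCF difference: d = (1 − m) × 0.3 + m × e
- SE = 1.2 × √(2/772) = 0.0611
- False-positive rate = Φ((0.3 − d)/SE − 2.2414)

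**Scenario (assumed).** The difference is 0 up to week 28, then rises linearly to 0.3 at week 104. Last observed visits are spread evenly over weeks 4, 12, 28, 40, 52, 65, 78 and 91. The differences at those visits are 0, 0, 0, 0.047, 0.095, 0.146, 0.197 and 0.249, so e = 0.092.

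| Missing (assumed) | d | (0.3 − d)/SE | Type I error | Multiple of 1.25% |
|---|---|---|---|---|
| 5% | 0.290 | 0.170 | 1.9% | 1.5 |
| 10% | 0.279 | 0.341 | 2.9% | 2.3 |
| 20% | 0.258 | 0.682 | 5.9% | 4.8 |
| 30% | 0.238 | 1.023 | 11% | 8.9 |

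With the planned 698 per arm (SE 0.0642) the same formula gives 1.9%, 2.8%, 5.6% and 10.2%.

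**Simulation check.** 698 per arm, 4,000 runs per scenario, visits of Table 2, ANCOVA with LOCF against a likelihood repeated-measures analysis with unstructured covariance. The true difference at the tested week is 0.3 throughout.

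| Pattern (assumed) | Missing | LOCF rejects | Repeated measures rejects |
|---|---|---|---|
| Week 104, 0 to 0.3 from week 28 | about 10%, 20%, 30% | 3.4%, 5.9%, 10.5% | 1.4% each |
| Same, with HbA1c-triggered rescue | 27% | 8.8% | 1.1% |
| Week 52, 0 to 0.3 from week 12 | 10%, 15% | 2.6%, 5.4% | 0.9%, 1.7% |
| Week 104, constant 0.3 | 10% to 29% | 1.0% to 1.4% | 0.9% to 1.2% |
| Week 104, glimepiride fades, 0.5 to 0.3 | 10% to 29% | 0.2% to 0.6% | 1.2% to 1.7% |

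Simulation error at the nominal level is about 0.2 points. The repeated-measures estimate was 0.298 to 0.301 in all scenarios. LOCF gave 0.237 to 0.278 in the first three rows and 0.314 to 0.341 in the last. In that last row it places empagliflozin too unfavourably, which is the same error that would hide an empagliflozin advantage in a superiority test. The data were generated to satisfy missing at random, so this check says nothing about other dropout mechanisms.

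**The case against.** **The documents expect the opposite fade.** A reader might infer that LOCF will make this trial's non-inferiority test too lenient. The article does not support that. It expects the sulfonylurea to lose effect, and under that pattern LOCF is stricter than nominal. Inflation requires empagliflozin to lose ground against glimepiride. This objection stands against any prediction of inflation. It does not remove the concern, because a type I error claim must also cover the unfavourable pattern, and in the expected pattern LOCF still gives the wrong estimate.

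**The size is assumed.** This stands. Neither the missing share nor the fade is in the article. At 5% missing the inflation in the scenario above is only about 1.5-fold, and with a constant difference there is none.

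**Other analyses could reveal the problem.** A reader might infer that only the MMRM could do so, because the completer analyses name LOCF too. That goes too far. FAS104 completers must have end-of-treatment HbA1c values, so LOCF can act there at most on values set to missing after rescue. These analyses offer a real comparison with the primary result. They also select patients on what happened after randomization, so they cannot replace a valid primary analysis.

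**MMRM has its own assumption.** It holds the level only under missing at random. Study design allows rescue on fasting glucose, or on HbA1c after week 28, and words it as something that can be initiated. Glucose is not in the model, and dropout for other reasons may depend on unobserved values. This stands and shapes the fix.

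**Conclusion.** The concern holds as a conditional one. The LOCF analysis does not target the week-52 or week-104 difference unless the treatment difference is stable, and the article gives its own reasons to expect that it is not.

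The bias can go either way. At week 104, late loss of empagliflozin's relative effect raises the type I error from 1.25% to between about 1.9% and 11% over 5% to 30% missing. At week 52 the inflation is smaller, about 2- to 4-fold at 10% to 15% missing. A stable difference leaves the level about nominal, and fading of glimepiride makes the test conservative while an empagliflozin advantage is understated at week 104. All these figures rest on assumed missing shares and trajectories, with the SD and margin taken from the article. No figure is given here for the loss of superiority power, because the article fixes no trajectory from which to calculate one.

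**What to change.** Before unblinded data are analysed:

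1. Make the already planned REML MMRM the primary analysis at weeks 52 and 104. Use on-treatment, pre-rescue HbA1c with treatment, visit, treatment-by-visit, eGFR category, region, baseline HbA1c and baseline-by-visit, and an unstructured covariance. Test each week's contrast against the 0.3% margin.
2. Keep the LOCF ANCOVA as a sensitivity analysis.
3. Add a missing-not-at-random sensitivity analysis, for example delta-adjusted or tipping-point imputation judged against the 0.3% margin.

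**Cost.** No new visits or data are needed, and the sample-size formula still gives 698 per arm. Two planned analyses change places and one is added. The price is that the primary result then relies on missing at random, which rescue guided by glucose and investigator discretion satisfies only approximately. Timing is the other limit. The article calls the 52-week analysis planned but does not say whether it has been run. If it has, the change is no longer a simple reordering.

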**Figure 1 F1:**
[figure not shown]
**Study design. ***Glimepiride was initiated at 1 mg/day, with the recommendation to uptitrate if fasting plasma glucose levels (assessed by home monitoring) were >110 mg/dL, to 2 mg/day at week 4, to 3 mg/day at week 8, and to a maximum of 4 mg/day at week 12. Uptitration can be withheld if it would place the patient at risk of hypoglycemia. Glimepiride dose can be downtitrated at any time to prevent recurrent hypoglycemia.

Patients received diet and exercise counseling at the beginning of the placebo run-in period based on local recommendations. Patients will be reminded about the importance of following the recommended diet and exercise plan at every study visit. Rescue therapy can be initiated during the 4-year treatment period if a patient has the following confirmed blood glucose levels after an overnight fast: >240 mg/dL during weeks 1 to 12, >200 mg/dL during weeks 12 to 28 and >180 mg/dL (or HbA1c >8%) after week 28. The choice and dosage of rescue medication are at the discretion of the investigator, but must not include an SU or SGLT2 inhibitor. The use of any anti-diabetes agents other than study medication, stable background metformin IR and rescue therapy is not permitted. There are no additional restrictions on the use of concomitant medications, except for those listed in the exclusion criteria (Table 1), which will be monitored throughout the trial.

The Clinical Trial Protocol was approved by the relevant Institutional Review Boards and local Independent Ethics Committees and the trial was conducted in accordance with the Declaration of Helsinki and the International Conference on Harmonization guidelines for Good Clinical Practice.

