## Results

Between August 2010 and June 2011, 1549 patients across 173 sites in 23 countries were randomized to receive study drug, of whom 1545 were treated. The baseline characteristics of the treated patients are shown in Table 4. The mean (SD) age was 55.9 (10.4) years, the mean (SD) HbA_1c,_ was 7.92 (0.84)% and the mean (SD) BMI was 30.11 (5.29) kg/m^2^. Mean (SD) systolic blood pressure was 133.5 (15.9) mmHg and mean (SD) diastolic blood pressure was 79.5 (9.4) mmHg, with 68.5% of patients having uncontrolled hypertension (≥130/80 mmHg).

**Table 4 T4:** Baseline characteristics (treated set: n=1545)

Gender, n (%)	
Male	854 (55.3)
Race, n (%)	
Caucasian	1017 (65.8)
Asian	507 (32.8)
Black/African-American	20 (1.3)
Hawaiian/Pacific Islander	1 (0.1)
Ethnicity, n (%)	
Non-Hispanic/Latino	1233 (79.8)
Hispanic/Latino	312 (20.2)
Region, n (%)	
Europe/South Africa	639 (41.4)
Asia	434 (28.1)
Latin America	276 (17.9)
North America	196 (12.7)
Age (years), mean (SD)	55.9 (10.4)
Time (years) since diagnosis of T2DM, n (%)	
≤1	172 (11.1)
>1 to 5	677 (43.8)
>5 to 10	425 (27.5)
>10	271 (17.5)
Body weight (kg), mean (SD)	82.8 (19.2)
Body mass index (kg/m^2^), mean (SD)	30.1 (5.3)
Body mass index (kg/m^2^), n (%)	
<25	243 (15.7)
25 to <30	587 (38.0)
30 to <35	434 (28.1)
≥35	281 (18.2)
Waist circumference (cm), mean (SD)	
Male	104.1 (13.0)
Female	98.8 (12.8)
HbA_1c_ (%), mean (SD)	7.9 (0.8)
HbA_1c_ (%), n (%)	
<8.5	1173 (75.9)
≥8.5	372 (24.1)
Fasting plasma glucose (mg/dL), mean (SD)	149.9 (33.9)^a^
HOMA-IR (mU/L x mmol/L), mean (SD)	6.03 (5.31)^b^
HOMA-B (mU/mmol), mean (SD)	77.0 (79.0)^c^
Cardiovascular medications, n (%)	1174 (76.0)
Antihypertensive agents	933 (60.4)
Lipid lowering agents	805 (52.1)
Acetylsalicylic acid	498 (32.2)
Systolic blood pressure (mmHg), mean (SD)	133.5 (15.9)
Diastolic blood pressure (mmHg), mean (SD)	79.5 (9.4)
Blood pressure controlled (<130/80 mmHg), n (%)	
Yes	486 (31.5)
No	1059 (68.5)
Serum lipids (mmol/L), mean (SD)	
Total cholesterol^d^	4.49 (1.01)
HDL-cholesterol^e^	1.25 (0.31)
LDL-cholesterol^f^	2.42 (0.86)
Triglycerides^e^	1.86 (1.29)
Markers of renal function and damage	
eGFR (mL/min/1.73 m^2^) according to MDRD, mean (SD)	88.0 (17.3)
eGFR (mL/min/1.73 m^2^) according to MDRD, n (%)	
≥90 (normal renal function)	633 (41.0)
60 to <90 (mild renal impairment)	877 (56.8)
30 to <60 (moderate renal impairment)	35 (2.3)
Urine albumin/creatinine ratio (mg/g), mean (SD)	40.22 (135.59)
Urine albumin/creatinine ratio (mg/g), n (%)	

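### Carrying forward the last blood pressure before an antihypertensive change can overstate the SBP and DBP difference, if the arms truly differ and the visit reading prompts the change

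*Protocol article*

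**What the plan says.** The blood pressure rule is in the Protocol article, Statistical analysis: "Blood pressure data after changes in antihypertensive medication will be set to missing and imputed using LOCF". It does not distinguish increases from decreases in therapy, or changes made because of blood pressure from changes made for other reasons.

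Change in SBP and change in DBP are listed as key secondary endpoints. In Table 3, SBP superiority is step 4 at week 52 and step 5 at week 104; DBP is step 5 and step 6. The key secondary tests are "based on a significance level of 2.5% (two-sided"). That makes two endpoints and four tests.

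Table 2 schedules 11 post-baseline blood pressure visits up to week 104. On other drugs, Study design says "There are no additional restrictions on the use of concomitant medications" beyond the exclusion list. At baseline 60.4% took antihypertensive agents (Table 4), and the Results describe the population "with 68.5% of patients having uncontrolled hypertension (≥130/80 mmHg").

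The sensitivity analyses that the article describes, including the MMRM, are for HbA1c. None is described for blood pressure.

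**The concern.** A reading that leads to a change in treatment is, on average, further from the patient's own mean than that patient's next reading would be. LOCF ignores this regression to the mean and enters the selected reading as the week-52 or week-104 value.

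If the arms do not differ, the error is the same in both and cancels. If empagliflozin lowers blood pressure, more glimepiride patients pass a high threshold and are fixed at high values. If low readings lead to reductions in therapy, more empagliflozin patients are fixed at low values. Both move the contrast towards empagliflozin.

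What is at stake is the size of the reported effect. The Background and Discussion present blood pressure lowering as a possible advantage of empagliflozin, so the estimate will be read as well as the p-value.

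**Working it through.** **The plan's own figure.** The only sample-size statement concerns HbA1c: "In total, 698 patients per arm are required to provide a power of ≥95% to show non-inferiority, based on a margin of 0.3"%. With a true difference of 0.05, SD 1.2 and one-sided 1.25%:

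n = 2 × (2.2414 + 1.6449)² × 1.2² / (0.3 − 0.05)² = 2 × 15.10 × 1.44 / 0.0625 ≈ 696 per arm.

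Power at 698 per arm is 95.06%. The figure reproduces, but it has no bearing on blood pressure, for which the article states no effect size or power.

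**Inputs from the article.** Baseline SBP 133.5 (SD 15.9) mmHg; visits at weeks 4, 8, 12, 16, 28, 40, 52, 65, 78, 91 and 104; 1545 treated patients, about 772 per arm; placebo-corrected SBP reductions of 2.1 to 4.8 mmHg (Background). The effect against glimepiride is not given, so this range stands in for it.

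**Assumptions not in the article.** Within-patient correlation ρ of 0.5 to 0.7; a change follows a visit SBP above 140, 150 or 160 mmHg with probability 0.1, 0.3 or 0.5 per visit respectively; an added drug lowers SBP by 10 mmHg; optionally, therapy is reduced after SBP below 110 mmHg.

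**Mechanism by hand.** For a reading above threshold t in an arm with mean μ, the average excess over μ is SD × φ(a)/(1 − Φ(a)), with a = (t − μ)/SD. LOCF keeps all of it, whereas a later reading would be expected to keep only the fraction ρ. The error per changed patient is therefore about (1 − ρ) × excess. Take t = 150, ρ = 0.5 and a true difference of −4.8:

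- Glimepiride, μ = 133.5: a = 1.04, excess 24.7, error 0.5 × 24.7 = 12.4 mmHg. Simulated share changed by week 104: 28.9%.
- Empagliflozin, μ = 133.5 − 4.8 = 128.7: a = 1.34, excess 28.7, error 14.3 mmHg. Share changed: 18.9%.
- Net: 0.289 × 12.37 − 0.189 × 14.34 = 3.57 − 2.71 = 0.86 mmHg in favour of empagliflozin.

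This ignores selection over repeated visits. Full simulation of the same case gave −5.80 under LOCF against −4.78 had no change occurred, an excess of 1.02 mmHg.

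**Simulation, week-104 SBP, baseline-adjusted ANCOVA (mmHg).**

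| Scenario | Value had no change occurred | Planned LOCF rule | All observed readings kept |
|---|---|---|---|
| Increases only, true −2.1 | about −2.1 | −2.1 to −2.7 | −1.7 to −1.8 |
| Increases only, true −4.8 | −4.8 | −5.0 to −5.9 | −3.8 to −4.3 |
| Increases and reductions (ρ 0.6, 150/110), true −2.1 | −2.13 | −2.88 | −1.33 |
| Increases and reductions (ρ 0.6, 150/110), true −4.8 | −4.78 | −6.37 | −3.02 |

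Relative overstatement against the no-change value:

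- Increases only: from 5.00/4.80 = 1.04 to 2.68/2.14 = 1.25.
- Both directions: 2.88/2.13 = 1.35 and 6.37/4.78 = 1.33.

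**Where the bias is absent.**

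- True difference 0: the LOCF difference is about 0. In 8000 simulated trials of 772 per arm, the rejection rate was 2.4% to 2.6% against the nominal 2.5%.
- Changes unrelated to blood pressure, true −3.0: LOCF gives −2.98.
- Changes prompted by a separate reading of the same patient (between-patient SD 13, visit-to-visit SD 9, both assumed): a true −4.0 is estimated as −3.9 to −4.1, even with 37% to 39% of patients changed.

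**Does the alternative work?** With visit-triggered changes and a true −4.0, LOCF gave about −4.1 to −5.1. An unstructured likelihood estimate on the same pre-change readings gave −3.9 to −4.1, including with autocorrelated errors.

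**DBP.** The mechanism is the same, but the article gives no DBP effect. With an assumed true −2.0 and thresholds of 85, 90 or 95 mmHg, LOCF gave −2.14 to −2.44.

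**The case against.** The deletion rule answers a reasonable question, and LOCF is the article's general method for efficacy data. That stands; only the LOCF step is open to criticism.

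The article does not say why antihypertensives are changed, or that the last visit reading is the trigger. Changes may follow readings taken elsewhere, side effects or substitution, and then the bias largely goes. The 60.4% and 68.5% are baseline prevalences, not change rates. They make changes plausible but give no frequency by arm. All of this stands, and it is why the point is conditional and its size is a range that includes negligible values. The upper end also needs reductions after low readings, for which the article gives no rate.

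The full protocol and analysis plan are not shown and may contain further blood pressure analyses. So the absence of a supportive analysis is not itself the point. The point is the method that the article does state.

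Two stronger readings are tempting. A reader might infer that the rule always exaggerates the difference; it does so only when a true difference exists and the carried-forward reading prompts the change. A reader might also infer that the confirmatory tests are invalid; with no true difference the rejection rate stays at its nominal level.

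**Conclusion.** The concern holds as a conditional bias in the size of the effect. Given a true blood pressure difference and changes prompted by the visit reading, the stated rule overstates that difference in favour of empagliflozin: by about 0.1 to 1.1 mmHg of SBP with increases in therapy only, and by up to about 1.6 mmHg, roughly a third of the effect, if low readings also lead to reductions. These sizes rest on assumed trigger thresholds, trigger probabilities and within-patient correlation, and on placebo-corrected effects standing in for the effect against glimepiride. This mechanism is not a source of false positives. The change is worth making because the article fixes the method for endpoints in both testing hierarchies, and a better one is already planned for HbA1c.

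**What to change.** Keep the rule that sets readings after an antihypertensive change to missing, and drop LOCF from the main SBP and DBP analyses. Use MMRM with unstructured covariance, the baseline value of the endpoint and the stratification factors, on all readings up to the change, with the contrast taken at week 52 or week 104.

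Keep the LOCF analysis as a sensitivity analysis. Add a supportive analysis of all observed readings regardless of antihypertensive change, and label it as answering a different question: it includes the effect of the added or reduced drugs, and in the simulations its estimate lay closer to zero than the no-change effect.

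The cost is a change of analysis wording; Table 2 already schedules the readings. The downside for the sponsor is that the estimated blood pressure effect may be somewhat smaller.

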### Study design

The protocol stated that patients were to be screened for eligibility for the study 21±7 days prior to randomization. Eligible patients were to undergo a 2-week, open-label, placebo run-in period prior to randomization, during which metformin IR was to be continued at the patient’s usual dose. Following the run-in period, patients still meeting the inclusion criteria were randomized 1:1 to receive empagliflozin 25 mg qd or glimepiride 1–4 mg qd in a double-blind, double-dummy manner for 2 years, in addition to metformin IR (Figure 1). Glimepiride was initiated at a dose of 1 mg/day, with the recommendation for uptitration if fasting plasma glucose (FPG) (assessed by home monitoring) was >110 mg/dL to 2 mg/day at week 4, to 3 mg/day at week 8, and to a maximum of 4 mg/day at week 12. Uptitration was to be withheld if it would place the patient at risk of hypoglycemia and should not take place after week 12. The glimepiride dose can be downtitrated at any time to prevent recurrent hypoglycemia. Randomization was achieved using a computer-generated random sequence communicated via a third-party interactive voice or web response system. Randomization was stratified by HbA_1c_ at screening (<8.5% and ≥8.5%), eGFR according to the Modified Diet Renal Disease (MDRD) formula (<90 mL/min/1.73 m^2^ and ≥90 mL/min/1.73 m^2^) and region (Europe/South Africa, Asia, North America, and Latin America). Patients who participate in the 2-year randomized treatment period are eligible to participate in a 2-year extension period, during which they will continue to receive the treatment allocated at randomization in a double-blind, double-dummy manner. All patients will be followed up for 4 weeks after the last dose of study drug.

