### List of study efficacy endpoints

Primary efficacy endpoints

Change from baseline in HbA_1c_ after 52 and 104 weeks of treatment

Key secondary endpoints

Change from baseline in body weight after 52 and 104 weeks of treatment

Occurrence of confirmed hypoglycemic AEs^†^ during 52 and 104 weeks of treatment

Change from baseline in SBP and DBP after 52 and 104 weeks of treatment

Exploratory endpoints

^†^Blood glucose ≤70 mg/dL and/or assistance required.

^‡^Calculated as slope of least-squares regression line including all measurements from week 28 to last available measurement.

*Legend*: *HbA*_*1c*_ glycosylated hemoglobin, *AEs* adverse events, *SBP* systolic blood pressure, *DBP* diastolic blood pressure, *FPG* fasting plasma glucose, *MDG* mean daily glucose, *PPG* post-prandial glucose, *MTT* meal tolerance test, *DXA* Dual Energy X-ray Absorptiometry, *VAT* visceral adipose tissue, *SAT* subcutaneous adipose tissue, *MRI* magnetic resonance imaging, *BP*: blood pressure.

*Glucose control*

HbA_1c_ <7.0% or <6.5% after 52, 104 and 208 weeks of treatment

HbA_1c_ lowering by ≥0.5% after 52, 104 and 208 weeks of treatment

Change from baseline in HbA_1c_ after 208 weeks of treatment

Coefficient of durability for HbA_1c_ response^‡^

Change from baseline in FPG after 52, 104 and 208 weeks of treatment

Change from baseline in MDG (8-point) after 52, 104 and 208 weeks of treatment (sub-study)

Change from baseline in 2-h PPG after 52, 104 and 208 weeks of treatment and follow-up (4 weeks after treatment discontinuation) (sub-study)

Biomarkers of insulin secretion and resistance after 104 and 208 weeks of treatment and (in the MTT sub-study) follow-up (4 weeks after treatment discontinuation)

Confirmed hypoglycemic AEs^†^ during 208 weeks of treatment

*Weight loss*

Change from baseline in body weight of >2% and >5% after 52, 104 and 208 weeks of treatment

Change from baseline in body weight after 208 weeks of treatment and follow-up (4 weeks after treatment discontinuation)

Change from baseline in waist circumference after 52, 104 and 208 weeks of treatment and follow-up (4 weeks after treatment discontinuation)

Changes from baseline in trunk fat, limb fat, fat-free mass and total fat mass (using DXA scan) after 52, 104 and 208 weeks of treatment (sub-study)

Changes from baseline in bone mineral density and T-scores (using DXA scan) after 52, 104 and 208 weeks of treatment (sub-study)

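### The confirmatory hypoglycemia test uses an HbA1c split alone and takes no account of time at risk: the strata cost little, and time at risk matters only if discontinuation differs by arm

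*Protocol article*

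**What the plan says.** All places are in the Methods of the protocol article.

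- **Endpoint.** The List of study efficacy endpoints gives, as a key secondary endpoint, "Occurrence of confirmed hypoglycemic AEs^†^ during 52 and 104 weeks of treatment".
- **Place in the hierarchy.** Table 3 has "Superiority in incidence of confirmed hypoglycemic AEs" at step 3 at both time points, tested at two-sided 2.5%. SBP and DBP follow it at week 52. HbA1c superiority, SBP and DBP follow it at week 104.
- **Test.** In Statistical analysis: "Confirmed hypoglycemic events will be analyzed using Cochran-Mantel Haenszel tests stratified by baseline" HbA1c, below 8.5% versus 8.5% or more. The sentence stands in the paragraph on safety endpoints in the treated set.
- **Randomization.** In Study design: "Randomization was stratified by HbA_1c_ at screening (<8.5% and ≥8.5%), eGFR according to the Modified Diet Renal Disease (MDRD) formula" (split at 90 mL/min/1.73 m²) and "region (Europe/South Africa, Asia, North America, and Latin America".
- **Primary model.** The ANCOVA has eGFR and region as fixed effects and baseline HbA1c as covariate. A general sentence extends this model to the secondary endpoints.
- **Rescue.** Efficacy data after the first rescue intake are set to missing.
- **Time-to-event methods.** Kaplan-Meier and log-rank are named for albuminuria only.

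**The concern.** Two features of a stated confirmatory method looked weak. First, the test adjusts for one factor, measured at baseline, where randomization used three, with HbA1c taken at screening. A test that drops prognostic randomization factors can lose precision. Second, a test of occurrence in a fixed window gives the same weight to a patient observed for 10 weeks without an event as to one observed for 104. If one arm loses more patients, it has less time in which to record events, and the comparison shifts in its favor. The article names time-to-event methods for albuminuria, which is outside the hierarchy, but none for this endpoint, which is in it.

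At stake are the hypoglycemia claim itself and the tests that follow it in each hierarchy.

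**Working it through.** **The plan's own figure.** No sample size or power is stated for hypoglycemia. The only figure, 698 per arm, is for HbA1c non-inferiority: n = 2 × (1.2/0.25)² × (2.241 + 1.645)² = 696, which agrees. Nothing below affects it.

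**Inputs from the article.** 1545 treated (about 772 per arm), two-sided level 2.5% (critical value 2.241), and the Table 4 margins: baseline HbA1c 75.9/24.1%, eGFR 90 or more 41.0%, regions 41.4, 28.1, 17.9 and 12.7%.

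**Assumptions.** Event rates, factor effects and dropout are not in the article. The factors are treated as independent.

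**1. Stratification.** Three factors give 2 × 2 × 4 = 16 cells, averaging 1545/16 = 97 patients. The smallest is about 1545 × 0.241 × 0.41 × 0.127 = 19. The CMH with 2 strata was simulated against the CMH with 16 (20,000 runs per setting). Strong factor effects mean odds ratios of 0.5, 2 and 4 for HbA1c, eGFR and region.

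| Setting | 2 strata | 16 strata |
|---|---|---|
| Power, 5% vs 10%, no factor effects | 93.7% | 93.8% |
| Power, 5% vs 10%, strong effects | 94.5% | 94.8% |
| Power, 5% vs 9%, no factor effects | 80.9% | 81.0% |
| Power, 5% vs 9%, strong effects | 81.2% | 81.7% |
| Type I error, 10% in both arms, all settings | 2.3–2.4% | 2.4–2.6% |

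The gain is at most 0.5 points of power.

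**2. Time at risk, effect on the proportion.** Let p be the true 104-week incidence under a constant hazard, so λ = −ln(1 − p) per 104 weeks. Let a fraction d leave at uniformly spread times, and count leavers without an event as non-events. The recorded proportion is

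q = (1 − d) × p + d × (1 − p/λ).

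For p = 0.22: λ = 0.2485 and 1 − p/λ = 0.1145.

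- d = 0.20: 0.176 + 0.0229 = 19.9%
- d = 0.15: 20.4%; d = 0.25: 19.4%; d = 0.30: 18.8%
- Risk ratio with no true difference: 0.948 for 25% vs 15%, and 0.923 for 30% vs 15%

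**3. Time at risk, effect on the error rate.** With equal true incidence, let δ = |q₁ − q₂| / SE, where SE = √(2q̄(1 − q̄)/772). The rejection probability is about Φ(δ − 2.241) + Φ(−δ − 2.241).

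Example with p = 0.20 and dropout 30% vs 15%: q = 0.1711 and 0.1856, SE = 0.0195, δ = 0.74, so the error is 0.067 + 0.001 = 6.8%.

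The last column below comes from simulating the two-stratum CMH with exponential instead of uniform leaving times. Its ranges cover either arm having the higher dropout.

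| True incidence, both arms | Dropout | Uniform leaving, formula | Exponential leaving, simulated |
|---|---|---|---|
| 10% | equal, 15 or 20% | 2.5% | 2.4% |
| 10% | 25% vs 15% | 3.3% | 3.4–3.6% |
| 10% | 30% vs 15% | 4.5% | 4.6–4.8% |
| 20% | equal, 15 or 20% | 2.5% | 2.4–2.5% |
| 20% | 25% vs 15% | 4.3% | 4.3–4.7% |
| 20% | 30% vs 15% | 6.8% | 7.6–7.8% |

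The 16-stratum test gives almost the same inflated figures (up to 7.9%), so adding strata does not cure this.

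**4. Power (simulated).** For a true 5% on empagliflozin vs 10% on glimepiride, power is 94.0% without dropout and 92.0% or 90.7% with equal dropout of 15% or 20%. It falls to 79.5% if 15% leave on empagliflozin and 30% on glimepiride. For 2% vs 20% it is 100% in every setting tried.

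**5. Events after rescue.** Hypoglycemia is listed among the efficacy endpoints, so the rule that removes efficacy data after rescue would apply. Its test is described with the treated-set safety analyses, where that rule need not apply. The general sentence giving secondary endpoints the primary model does not settle it, since a CMH test is not that ANCOVA.

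**The case against.** The best defense is that the test fits the endpoint. Occurrence in a window is binary, Table 3 speaks of incidence, and a CMH test on one prognostic factor is valid. Using baseline HbA1c is consistent with the primary ANCOVA. Time to first event answers a different question and needs non-informative censoring. All of this stands, and it is why the CMH need not be replaced.

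Three stronger readings are tempting and not supported:

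- A reader might infer that the plan counts early leavers as event-free for 104 weeks. The article states no such rule. It is how a plain yes/no test on all treated patients would behave unless another rule applies. It could concern only patients who leave before any event, and the full protocol or analysis plan may deal with it.
- A reader might infer that events after rescue count. The article points both ways.
- A reader might infer that leaving out the strata does serious harm. The simulation shows under 1 point of power.

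The size of the time-at-risk effect also rests wholly on assumed inputs. A constant hazard is doubtful, because glimepiride uptitration ends at week 12 and downtitration is allowed for recurrent hypoglycemia. If events come early, the bias shrinks. Its direction depends on which arm loses more patients, which the article cannot show.

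What remains is that the stated test has no protection against unequal discontinuation, and no supportive analysis is named that would reveal the problem.

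**Conclusion.** The concern holds as a robustness weakness in a stated method. It is not an error in the test. The stratification mismatch is real but costs under 1 point of power and leaves type I error near 2.5%. Ignoring time at risk does no harm to type I error under equal dropout. Under a 10 to 15 point gap it takes the nominal 2.5% to roughly 3.3 to 7.8%, assuming 10 to 20% event rates, constant hazards and event-free leavers counted as non-events. If glimepiride loses more patients, power falls instead. A very large true difference would make both points immaterial. The handling of events after rescue is unresolved in the text. The change is worth making because the endpoint is confirmatory, later tests follow it, and the cost is small.

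**What to change.** 1. Keep the CMH test of occurrence, but stratify it by the three randomization factors as randomized: screening HbA1c, eGFR and region.
2. Prespecify a supportive analysis of time to first confirmed event (log-rank and Cox, stratified by the same factors), censored at end of treatment, with one version censored at first rescue.
3. Reconcile the efficacy-endpoint listing, the rule on data after rescue and the treated-set safety paragraph, so that it is clear which analysis set and which handling of events after rescue apply to this test.

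The cost is one extra model and a few lines of wording, with no new data. Some of the 16 strata will be sparse (smallest about 19 patients), which the CMH tolerates. The time-to-event analysis assumes non-informative censoring, which is a reason to keep it supportive.
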